### Interventions

2.8

The participants in the control group will be provided nutrition counseling on recommended chemotherapy, radiation, postoperative, and cancer-preventive diets. In addition to nutrition counseling, participants in the YGJT group will be administered YGJT at a dose of 3 g twice a day before meals for 4 weeks, for a total of 56 doses of 3.0 g per dose. Kolmarpharma Co, Ltd, produces the YGJT in accordance with Korea Good Manufacturing Practice (KGMP) standards. YGJT is manufactured by spray-drying a hot water extract of a mixture of 8 varieties of the following crude drugs: Atractylodis lanceae rhizoma (4.0 g), Ginseng radix (4.0 g), Pinelliae tuber (4.0 g), Poria cocos (4.0 g), Zizyphi fructus (2.0 g), Aurantii nobilis pericarpium (2.0 g), Glycyrrhizae radix (1.0 g), and Zingiberis rhizoma (0.5 g). These raw materials will be extracted and concentrated to 3 g per dose. The daily doses follow the recommended dosage method of the Korea Ministry of Food and Drug Safety (MFDS). During the trial, participants will be prohibited from receiving any other treatment for anorexia.

### Outcome measurement

2.9

#### Primary outcomes

2.9.1

The primary outcome is the change in the score on the anorexia/cachexia subscale (A/CS) of the Functional Assessment of Anorexia/Cachexia Therapy (FAACT) between baseline (visit 2) and the end of the administration period (visit 4). The FAACT is a clinical questionnaire for assessing the general aspects of QOL, as well as specific anorexia-related concerns, in patients with cancer. Especially, the A/CS has 12 items focusing on anorexia and cachexia among the total 39 items. The Korean version of FAACT, which was translated by the Functional Assessment of Chronic Illness Therapy (FACIT) organization, will be used. A trained investigator using standards operating procedures (SOPs) will determine and record the A/CS score at each visit.

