### Withdrawal criteria

2.5

Participants who meet the withdrawal criteria will be dropped from the trial. Participants who withdraw or are dropped after randomization will be followed for outcomes. The withdrawal criteria include the use of any forbidden medication or treatment during the trial that could affect the study result, the participant's withdrawal of consent, the occurrence of a serious adverse event, the detection of eligibility violations, the occurrence of other significant protocol violations during the trial, and the investigator's decision to terminate the process for the sake of the participant's health.

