### Sample size

2.6

This study is an exploratory trial conducted before a confirmatory trial to establish the validity of using YGJT to treat patients with cancer who are suffering from anorexia. The efficacy of YGJT will be examined in order to provide information that will lead to a better design for a future clinical trial. Considering a dropout rate of 20%, we calculated that a total of 52 subjects, 26 per group, should be enrolled in this study. The sample size was set using an effective size of 0.9, which is the ratio of the standard deviation of each group from the mean difference of outcomes between the YGJT group and the control group at a significance level of 5% and a power of 80%. The formula for estimating the sample size is as follows:  

where n is the approximate sample sizes required per group, *t*_*α,v*_ is the 97.5 percentile score of the *t* distribution with *v* degrees of freedom, and *t*_*β*(1),*v*_ is the 80 percentile score of the *t* distribution with *v* degrees of freedom. If *v* = 40, n′ ≥ 2 × 1.2346 × (2.0211 + 0.8507)^2^ = 20.3632 (21). For a dropout rate of 20%, the sample size for each group is given by n = 21 × 1.2 = 25.2 (26). Therefore, a total of 52 subjects, 26 in each of the 2 groups, will be enrolled in this study.

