#### Efficacy assessment

2.10.1

The Shapiro–Wilk test will be used to test normality for the mean changes of primary and secondary outcomes between baseline (visit 2) and the end of treatment (visit 4). A significance level 0.05 will be used to test the differences between the 2 groups. The statistical significance of the variables in 2 groups will be tested by using either the paired *t* test or the Wilcoxon signed rank test. The present study has no plans for interim analysis.

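### The stated efficacy test uses only the visit 2 to visit 4 change in A/CS, so it does not adjust for baseline and gives the score recorded in between no role (optional improvement)

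*Protocol article*

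**What the plan says.** All references are to the protocol article.

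- **Primary outcomes (2.9.1)** takes the A/CS change "between baseline (visit 2) and the end of the administration period (visit 4"), and adds that a trained investigator "will determine and record the A/CS score at each visit".
- **Efficacy assessment (2.10.1)** checks normality of the "mean changes of primary and secondary outcomes between baseline (visit 2) and the end of treatment (visit 4") and then says: "The statistical significance of the variables in 2 groups will be tested by using either the paired" t test or the Wilcoxon signed rank test. It names no other visit, no baseline covariate and no longitudinal model.
- **Sample size (2.6)** states: "Considering a dropout rate of 20%, we calculated that a total of 52 subjects, 26 per group, should be enrolled". It adds: "The sample size was set using an effective size of 0.9".
- **Withdrawal criteria (2.5)** states: "Participants who withdraw or are dropped after randomization will be followed for outcomes". Withdrawal of consent is among the listed reasons.

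The visit timetable (Table 1) is not shown. That there is a visit 3 with an A/CS score follows from the visit numbering and the each-visit statement.

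**The concern.** A test on one change score needs both scores. A patient without a visit-4 score can enter only if that score is imputed, and the visit-3 score is not used by the test itself. A raw change score also fixes the weight of the baseline at 1 instead of estimating it, which costs precision unless baseline and final score are very highly correlated.

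Two things could be at stake. The first is precision, in a trial with about 21 evaluable patients per arm. The second is bias, if patients leave for reasons linked to arm and response. Such a link is plausible here. Study design calls the trial double-blind, but the control arm receives counselling only, with no placebo described, and Randomization and allocation says patients will be told their allocation. Other treatment for anorexia is prohibited, and using a forbidden treatment is a ground for withdrawal. A control patient who is not improving therefore has a reason to leave, and the visit-3 score would carry information about it.

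**Working it through.** **1. The plan's own figure.** Inputs from Sample size: effect 0.9 SD, two-sided 5%, power 80%, *v* = 40.

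- 2/0.9² = 2 × 1.2346; 2 × 1.2346 × (2.0211 + 0.8507)² = 20.36, rounded up to 21.
- 21 × 1.2 = 25.2, rounded up to 26 per arm, 52 in total. This reproduces.
- If 20% of 26 have no visit-4 score, 26 × 0.8 = 20.8 per arm remain. Power from the non-central t distribution is 79.2% with 20 per arm, 80.8% with 20.8 and 81.2% with 21. The planned power is essentially kept.

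**2. Precision.** The documents give no correlations or dropout timing. Assumed: unit SD at each visit; correlations 0.6 (visits 2 and 3), 0.5 (2 and 4) and 0.7 (3 and 4); 20% without a visit-4 score, 8 points of it lost before visit 3; dropout at random. Each analysis has a closed-form check and a simulation of 8,000 trials.

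- *Change score.* Variance 2(1 − 0.5) = 1, so SE = √(2/20.8) = 0.310. Simulated: 0.316.
- *ANCOVA on completers.* Factor √(1 − 0.5²) = 0.866, and 0.316 × 0.866 = 0.274. Simulated: 0.275.
- *Model with visit 3.* Correlation of visits 3 and 4 given baseline: (0.7 − 0.6 × 0.5)/√((1 − 0.36)(1 − 0.25)) = 0.4/0.693 = 0.577, squared 0.333. With 26 × 0.92 = 23.92 per arm at visit 3, the variance factor is 1 − 0.333 × (23.92 − 20.8)/23.92 = 0.957, and 0.275 × √0.957 = 0.269. Simulated: 0.268.

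Repeat simulations gave 0.305 to 0.316, 0.269 to 0.276 and 0.263 to 0.269. Of the total fall in SE, (0.316 − 0.275)/(0.316 − 0.268) = 85% comes from baseline adjustment. Visit 3 then adds 1 − (0.268/0.275)² = 5% in variance.

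**3. Power from visit 3 alone, without baseline adjustment.** Variance = (s²/n₄)[1 − r²(n₃ − n₄)/n₃], where n₃ and n₄ are the numbers per arm with a score and r is the correlation of the visit-3 and visit-4 changes. Assumed: r from 0.3 to 0.8, with 50% to 100% of dropouts reaching visit 3.

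- With 20.8 completers, effective n is 21.0 to 23.9 and power 81.2% to 86.0%, against 80.8%.
- With 20 completers, power is 79.7% to 85.5%, against 79.2%.

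The gain is about 0.4 to 6 percentage points.

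**4. Bias.** Same correlations, no true effect. After visit 3, controls who worsened leave with probability 35% and other controls with 5%; the YGJT arm loses 13%. With half of the controls worsening by chance, loss in that arm is 0.08 + 0.92 × 0.20 = 26%, against 0.08 + 0.92 × 0.13 = 20%. Mean estimated difference, YGJT minus control, in SD:

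| | Change score | ANCOVA | Model with visit 3 |
|---|---|---|---|
| All who drop out lack visit 4 | −0.093 | −0.063 | −0.003 |
| Half of them still measured at visit 4 | about −0.04 | about −0.025 | about 0 |

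Monte Carlo error is about 0.316/√8000 = 0.004, so −0.003 is compatible with zero. Repeat runs gave −0.09 to −0.10 for the change score. Against the planned effect, 0.093/0.9 = 10%; against its own SE, 0.093/0.316 = 0.29. The sign is negative: when worsening controls leave, the remaining controls look better.

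**The case against.** The strongest case against is that this rests on silence. The article never says that visit-3 scores are thrown away or that only completers are analysed. It condenses a fuller protocol (version 2.2), which is not shown, and an analysis plan may exist. Imputation rules, analysis sets and sensitivity analyses commonly sit there. That stands, so the absence of a missing-data rule is not part of this point. What remains is the method that the article does state: a test on one change score.

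A reader might infer that visit-3 data are discarded and that one patient in five contributes nothing. The documents do not support this. Withdrawn participants are to be followed for outcomes, so 20% dropout need not mean 20% missing. Some, such as those who withdraw consent, may still have no visit-4 score.

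It is also fair that an end-of-treatment change is a legitimate endpoint, that the trial is exploratory, and that the enrolment allowance already protects power. The allowance does nothing about bias, however.

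Finally, the size rests on assumptions. Dropout in the scenario depends on the visit-3 score, which is the setting where a model using that score is unbiased by construction. Dropout driven by changes after visit 3 would not be fully corrected. Nor should a reader infer that the stated test would exaggerate the benefit of YGJT: in the one scenario examined, the bias goes the other way.

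**Conclusion.** The point holds as an optional, low-cost improvement to a stated analysis. It is not an error in any stated figure: 21, 26 and 52 reproduce, and about 79% to 81% power is kept with 20% missing.

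Under the assumed correlations and 20% missing, the SE of the arm difference would fall from about 0.316 to 0.268 SD, mostly through baseline adjustment. If dropout depends on arm and visit-3 score, a bias of up to about 0.1 SD, or about 0.04 SD with half of those who drop out still measured, would also be removed. Correlations, dropout timing and differential dropout are all assumed, so these sizes are illustrative.

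**What to change.** Keep the visit-4 endpoint and the follow-up of withdrawn participants. State the primary analysis as a mixed model for repeated measures on A/CS at visits 3 and 4:

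- terms for arm, visit, arm by visit, baseline A/CS and baseline by visit;
- unstructured covariance and Kenward-Roger degrees of freedom;
- all randomised patients with any post-baseline score;
- the arm difference at visit 4, with its 95% confidence interval, as the reported result.

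Confirm from Table 1 that the A/CS is scored at visit 3. If it is not, ANCOVA on visit 4 with baseline as covariate gives most of the precision gain.

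The cost is analysis wording and a little programming; no new data are needed. The downside is one further modelling assumption and slightly more complexity. Efficacy assessment also names paired and signed-rank tests for a comparison of two independent groups. That is a separate and clearer defect, and both changes can be made in the same edit.

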#### Secondary outcomes

2.9.2

Secondary outcomes are the changes in the FAACT score with the A/CS score omitted, in the VAS scorer for appetite, in the weight and the body mass index (BMI), and in the levels of leptin, tumor necrosis factor-α (TNF-α), ghrelin, and IL-6. The study schedule is summarized in Table 1.

**Table 1 T1:**
[figure not shown]
Summary the timetable for the YGJT clinical trial.

#### Safety outcomes

2.9.3

All variables related to the safety assessment, such as vital signs; electrocardiography, CBC, chemistry, and urine test results; and adverse events, will be documented on the case report form (CRF) at every visit.

#### Subgroup analysis

2.9.4

Participants will be subdivided into the following 3 subgroups: patients who complain of anorexia after surgery, patients who complain of anorexia during radiation therapy or recent radiation therapy, patients who complain of anorexia more than 1 month after chemotherapy. Comparisons of the YGJT group and the control group will also be performed at the subgroup level.

### Statistical analysis

2.10

#### Efficacy assessment

2.10.1

The Shapiro–Wilk test will be used to test normality for the mean changes of primary and secondary outcomes between baseline (visit 2) and the end of treatment (visit 4). A significance level 0.05 will be used to test the differences between the 2 groups. The statistical significance of the variables in 2 groups will be tested by using either the paired *t* test or the Wilcoxon signed rank test. The present study has no plans for interim analysis.

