#### Subgroup analysis

2.10.3

The efficacy of YGJT between subgroups will be evaluated as follows: comparison of the YGJT efficacy for each of the subgroups in the YGJT group with that of the corresponding subgroup in the control group and comparison of the YGJT efficacy among the 3 subgroups of the YGJT group. The statistical significance of any differences between the YGJT group and the control group, among the 3 subgroups, will be analyzed using a generalized linear model with either the Wilcoxson rank sum test or the Kkruskal–Wallis test. All tests will be 2-sided tests, and the significance level will be 0.05.

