Even though this trial may provide scientific evidence for the efficacy of YGJT in relieving anorexia, this study has limitations that are mostly derived from its relatively small sample sizes. In addition, identifying clearly whether anorexia resulted from cancer or from cancer treatment, such as surgery, chemotherapy, or radiotherapy, is problematic. Therefore, the particular mechanisms underlying anorexia suffered by cancer patients cannot be clearly determined. Considering recruitment feasibility, patients with various cancer types and with different stages of cancer will be recruited in this pilot study. Further studies are needed to estimate the influences of both the specific types and stages of cancer and the surgical status. Despite these limitations, this study should serve as a pilot report to plan further clinical trials on herbal medicine and cancer-related anorexia.

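### The primary efficacy analysis names within-arm tests on unadjusted change, with a normality pre-test; a prespecified between-group ANCOVA on baseline A/CS would answer the question and usually be more efficient

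*Protocol article*

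**What the plan says.** Section 2.9.1 of the protocol article defines the endpoint: "The primary outcome is the change in the score on the anorexia/cachexia subscale (A/CS") of the FAACT, from visit 2 to visit 4. A trained investigator "will determine and record the A/CS score at each visit", so the baseline value will be in the data set.

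Section 2.10.1 sets out the efficacy analysis in three steps:

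- Shapiro–Wilk is used to "test normality for the mean changes of primary and secondary outcomes between baseline (visit 2) and the end of treatment".
- The stated aim is between groups: "A significance level 0.05 will be used to test the differences between the 2 groups".
- The tests are then named: "The statistical significance of the variables in 2 groups will be tested by using either the paired" t test or the Wilcoxon signed rank test.

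No baseline covariate appears. The generalized linear model in section 2.10.3 is for subgroups and names no baseline covariate either. For safety, section 2.10.2 does draw the distinction: two-sample t or Mann–Whitney between groups, paired t or signed rank within a group.

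**The concern.** There are three linked weaknesses in section 2.10.1.

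First, the named tests do not match the question. A paired t or signed rank test asks whether one arm changed from visit 2 to visit 4. Both arms receive nutrition counselling and both may improve, so a significant change within the YGJT arm says nothing about the effect of YGJT. Comparing the two within-arm p-values is not a test of the difference.

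Second, change is analysed without baseline adjustment. Subtracting baseline does not remove its influence: if the correlation r is below 1, patients with worse baseline scores tend to improve more, and a fraction (1 − r) of any chance baseline difference between arms passes into the estimate. With 26 per arm and no stratification factor named, this deserves attention, and precision is given away.

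Third, the evident purpose of the Shapiro–Wilk step is to choose between a t test and a rank test. The primary test, and with it the quantity tested, then depends on the data. Section 2.6 says the trial is to inform the design of a confirmatory trial; for that, a mean difference with its interval is more useful than a rank p-value.

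**Working it through.** **The plan's own figure.** Section 2.6: "The sample size was set using an effective size of 0.9", two-sided 5%, 80% power, 40 degrees of freedom.

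n = 2 × (1/0.9²) × (2.0211 + 0.8507)² = 2 × 1.2346 × 8.247 = 20.36, rounded up to 21. Then 21 × 1.2 = 25.2, rounded up to 26 per arm, 52 in total. The figure reproduces. It is a two-sample calculation, whereas section 2.10.1 names paired tests.

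**Comparator.** The fair comparator for ANCOVA is an unadjusted two-sample t test on change, which section 2.10.1 does not name for efficacy. With 21 per arm and d = 0.9, the noncentrality is 0.9 × √(21/2) = 2.92 on 40 df, and power is 0.812.

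**ANCOVA.** Assume equal SDs σ at both visits and correlation r.

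- Variance of change: 2σ²(1 − r).
- Residual variance given baseline: σ²(1 − r²).
- Ratio: (1 − r²) / [2(1 − r)] = (1 + r)/2.
- Small-sample penalty for estimating the slope: 1 + 1/(2n − 4) = 1 + 1/38 = 1.026 at n = 21.
- Effective effect size: 0.9 / √(ratio × penalty), on 2n − 3 = 39 df.

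| Assumed r | (1 + r)/2 | With penalty | Effective d | Power, 21 per arm | Evaluable n per arm for 80% |
|---|---|---|---|---|---|
| 0.3 | 0.650 | 0.667 | 1.10 | 0.936 | 15 |
| 0.5 | 0.750 | 0.770 | 1.03 | 0.900 | 17 |
| 0.7 | 0.850 | 0.872 | 0.96 | 0.861 | 19 |
| 0.9 | 0.950 | 0.975 | 0.91 | 0.821 | 20 |
| 0.95 | 0.975 | 1.001 | 0.90 | 0.811 | 21 |
| 0.99 | 0.995 | 1.021 | 0.89 | 0.804 | 21 |

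Against 0.812 and 21 per arm unadjusted, the gain is material at moderate r, nil near 0.95 and a slight loss above that.

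**Chance baseline imbalance.** The SD of the baseline difference between arms is √(2/26) = 0.28 SD. The chance that it exceeds 0.3 SD in either direction is about 28%. At an assumed r of 0.5, an imbalance of 0.3 SD shifts the change-score difference by (1 − 0.5) × 0.3 = 0.15 SD.

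**Pre-test.** This was simulated with 3,000 runs per setting and 21 per arm, using two-sample t or Mann–Whitney according to Shapiro–Wilk, with normal or exponential (strongly skewed) errors. Type I error of the two-stage procedure ranged from 0.046 to 0.060. Power at d = 0.9 was:

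| r | Errors | Two-stage | ANCOVA |
|---|---|---|---|
| 0.3 | normal | 0.811 | 0.935 |
| 0.3 | skewed | 0.855 | 0.923 |
| 0.5 | normal | 0.818 | 0.907 |
| 0.5 | skewed | 0.877 | 0.880 |
| 0.7 | normal | 0.831 | 0.877 |
| 0.7 | skewed | 0.900 | 0.862 |

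**Paired tests as written.** Suppose YGJT has no effect and both arms improve by 0.5 SD of change. With 21 per arm, the paired t test in the YGJT arm is significant with probability 0.587. The two arms disagree on significance with probability 2 × 0.587 × 0.413 = 0.485.

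**The case against.** The strongest reply is that no invalid result follows from leaving out the covariate. Allocation is 1:1, blocked and concealed, so a between-arm comparison of unadjusted change is unbiased over randomisation and keeps its error rate. The trial is exploratory, and the planned 21 per arm already gives 0.81 power for the assumed effect. This stands: the adjustment point is about efficiency.

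A reader might infer more than the article supports:

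- **That the change-score analysis is biased.** It is not. A chance baseline difference moves the estimate in the trial as realised, but that is not bias of the method.
- **That a material imbalance is likely.** The figure is about 28% for more than 0.3 SD.
- **That the pre-test inflates type I error.** The simulation shows no material inflation.
- **That ANCOVA costs nothing and always wins.** It costs a degree of freedom and about 2.6% in variance, and it lost to the two-stage procedure with strongly skewed errors at r = 0.7.
- **That adjustment deals with case mix.** The Discussion says "patients with various cancer types and with different stages of cancer will be recruited in this pilot study"; adjusting for baseline A/CS corrects imbalance in A/CS only.

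It can also be said that covariates and sensitivity analyses are often left to an analysis plan, which is not shown. But section 2.10.1 does not leave the method open. It names the tests, and those do not compare the groups. This may be a slip of wording, since section 2.10.2 makes the distinction correctly, but the text needs correcting either way. That the pre-test selects the test is not stated outright; it is the natural reading.

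**Conclusion.** The point holds in a limited form. As written, section 2.10.1 gives no test of the stated between-group hypothesis, makes no use of a baseline score that is collected, and sets a normality test in front of the primary analysis. The mismatch between the tests and the question is an error in the text. The missing adjustment is a loss of efficiency.

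The size of that loss rests on three assumptions: that 0.9 is in SDs of change (section 2.6 does not say so), that SDs are equal at the two visits, and a value of r that the article does not give. On these, power at 21 evaluable per arm would rise from 0.81 to about 0.94, 0.90 or 0.86 at r = 0.3, 0.5 or 0.7, with nothing gained near r = 0.95. The objection to the pre-test is that it leaves the primary test dependent on the data, not that it has been shown to inflate error.

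**What to change.** In section 2.10.1, replace the sentence naming the tests with a prespecified between-group analysis:

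- **Primary:** ANCOVA of visit-4 A/CS (or change in A/CS) on treatment group with baseline A/CS as covariate. Report the adjusted mean difference with its 95% CI.
- **Normality gate:** remove it.
- **Sensitivity:** the rank-sum (Mann–Whitney) test on change, reported whatever the distribution looks like.
- **Paired tests:** if kept, label them as within-arm description that carries no inference about YGJT against control.

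This needs no further patients, visits or measurements. The downside is one degree of freedom, a variance penalty of about 2.6% at 21 per arm, and possibly lower power than a rank test if errors are strongly skewed; the fixed sensitivity analysis would show whether the conclusion depends on that.

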### Study design

2.1

This study is a double-blind, randomized, controlled trial that aims to examine the efficacy and the safety of using YGJT to treat patients with cancer-related anorexia. All patients fulfilling the eligibility criteria will be selected. The enrolled participants will be randomly allocated to 2 groups: The control group will receive nutrition counseling, and the YGJT group will receive nutrition counseling and be administered YGJT. Figure 1 shows the schematic flow of this YGJT clinical trial.

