### Randomization and allocation

2.7

After informed consent has been obtained, random assignment will be performed by using a computer-generated, blocked, random-allocation sequence with an allocation ratio of 1:1. Each participant will be assigned to either the YGJT group or the control group according to a pregenerated randomization table and an assigned randomized number, which will be prepared in advance. Computer-generated block randomization, with block sizes of 4 and 8, will be done by a member of the Department of Information and Statistics, Chungnam National University, Daejeon, Korea; that member will have no clinical involvement in the trial. This procedure will ensure that the allocation is securely concealed from the researchers who will subsequently inform the patients of their allocations.

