#### Safety assessment

2.10.2

Adverse events (AEs) will be reported and recorded in detail during the entire study. The following will be used to assess safety: vital signs, CBC, chemistry, and urine tests, and electrocardiography. Safety-related variables will be analyzed using the intention to treat (ITT) data set. Comparisons between the ratio of the number of participants who experienced 1 or more adverse events to the total number in that group or subgroup will be performed using a chi-square analysis or Fisher exact test. The statistical significance of the changes between subgroups/groups will be tested using the 2-sample *t* test or the Mann–Whitney test. In addition, the statistical significance of changes within each group will be tested using the paired *t* test or Wilcoxon singed-rank test. Electrocardiography results and some urine-test results will be classified as normal and abnormal according to clinical significance, and comparisons within groups will be analyzed using the McNemar test.

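### Section 2.10.1 announces a between-group efficacy test but names only paired tests for it, in conflict with sections 2.6 and 2.10.2

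*Protocol article*

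**What the plan says.** - **Design.** Section 2.1: "The enrolled participants will be randomly allocated to 2 groups". Section 2.7 specifies a "blocked, random-allocation sequence with an allocation ratio of 1:1". Neither section describes matching or crossover.
- **Efficacy analysis.** Section 2.10.1 checks normality of the visit 2 to visit 4 changes with the Shapiro-Wilk test and then sets the aim: "A significance level 0.05 will be used to test the differences between the 2 groups". The next sentence names the tests: "The statistical significance of the variables in 2 groups will be tested by using either the paired" t test or the Wilcoxon signed rank test. It names no other test for the primary or secondary outcomes.
- **Safety analysis.** Section 2.10.2 treats the two questions separately. Between groups: "The statistical significance of the changes between subgroups/groups will be tested using the 2-sample" t test or the Mann-Whitney test. Within groups: "the statistical significance of changes within each group will be tested using the paired" t test or the signed-rank test.
- **Subgroups.** Section 2.10.3 names rank-sum and Kruskal-Wallis tests, but only for the subgroup comparisons.
- **Sample size.** Section 2.6 rests on the difference in mean outcome between YGJT and control relative to the standard deviation (0.9), "where n is the approximate sample sizes required per group", with v = 40.

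**The concern.** A paired test needs two linked measurements. In this trial the natural link is a patient's own baseline and visit 4 value, so a paired test answers whether patients in one arm changed. It does not answer whether YGJT adds anything to nutrition counselling, which is the question the randomisation was set up to answer.

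The distinction matters here because both arms receive counselling and entry requires an anorexia VAS score of at least 40 mm. Improvement without any YGJT effect is therefore plausible, through counselling, recovery or regression to the mean. A within-arm test counts that improvement in full, whereas a between-group test removes what the arms share. Someone programming the analysis literally from section 2.10.1 would have no valid, reproducible test of YGJT against control for the primary outcome.

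**Working it through.** **1. Which test the sample size belongs to.** Inputs from section 2.6: effect size 0.9, two-sided 5%, power 80%, v = 40.

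n = 2 × (1/0.9²) × (t₀.₉₇₅,₄₀ + t₀.₈₀,₄₀)² = 2 × 1.2346 × (2.0211 + 0.8507)² = 20.36, rounded up to 21 per group.

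This reproduces the plan's figure. The factor 2 and v = 2 × 21 − 2 = 40 are those of two independent samples. A paired t test at a standardised change of 0.9 would need only 12 pairs (power 81.0%), so the trial was not sized for a paired test.

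**2. Power of the two-sample test.** Noncentrality 0.9 × √(21/2) = 2.916 with 40 degrees of freedom gives 81.2% at 21 per group. At 26 per group the power is 88.9%. The stated N already fits a two-sample test.

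**3. Reading A: patients matched arbitrarily across arms.** The difference between two unrelated patients has SD √2 times that of one, so the standardised difference is 0.9/√2 = 0.636. Noncentrality is 0.636 × √21 = 2.916, as in step 2, but with only 20 degrees of freedom. Power is 79.2%. If the matching ignores outcome, the type I error stays at 5%. The cost is about 2 percentage points of power and a p-value that depends on how patients happen to be matched.

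**4. Reading B: before-after test within each arm.** Assume no YGJT effect, the same mean change m in both arms (in SDs of the change) and 21 evaluable per arm. With p the rejection probability of a two-sided 5% paired t test (noncentrality m√21, 20 degrees of freedom), the YGJT arm is significant with probability p. The pattern of YGJT significant and control not has probability p(1 − p).

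| Shared change m (SD) | YGJT arm significant | YGJT significant, control not |
|---|---|---|
| 0 | 5% | 5% |
| 0.2 | 14% | 12% |
| 0.4 | 42% | 24% |
| 0.5 | 59% | 24% |
| 0.7 | 86% | 12% |
| 0.9 | 97% | 2% |

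The documents give no value for m, so the whole range is shown. The last column can never exceed 25%, because p(1 − p) peaks at p = 0.5. The values at 0.4 and 0.5 SD are close to that ceiling and should not be taken as typical.

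**5. Whether another section supplies the test.** The two-sample sentence in section 2.10.2 sits under safety assessment, and the rank-sum test in section 2.10.3 serves the subgroups. Neither covers overall efficacy.

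**The case against.** The strongest reply is that section 2.10.1 makes two separate statements. One sets the level for the group comparison and the other describes before-after tests in each arm. Section 2.10.2 uses the same paired tests in just that sense. The between-group test would then merely be unnamed, which is acceptable in a condensed article whose statistical analysis plan is not shown.

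That reading is possible, but the text does not secure it. The sentence does not say within each group, it directly follows the between-group aim, and it is the only statement of tests for overall efficacy. The fault is that the wrong class of test is named where the between-group test belongs. An analysis plan that follows the article inherits the fault, and one that departs from it contradicts the article.

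Part of the reply stands. A reader might infer that the trial will judge YGJT by whether A/CS improves within the YGJT arm, and that its type I error is therefore uncontrolled. The documents do not support this. Nothing makes within-arm significance the success criterion, section 2.6 is built on the between-group difference, and section 2.9.4 says the groups will also be compared within subgroups, which presupposes an overall comparison. Under arbitrary matching the 5% level is kept. It is also fair that the trial calls itself exploratory and a pilot, and that section 2.10.2 shows the authors know the distinction, so a drafting slip is likely.

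**Conclusion.** The point holds as an internal contradiction in the primary analysis. Section 2.10.1 sets a between-group aim and names only paired tests, against the protocol's own usage in section 2.10.2 and its sizing in section 2.6. Either the announced comparison has no test, or it relies on an arbitrary matching of patients.

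The size depends on the reading. With arbitrary matching, the level is kept, power falls from 81.2% to 79.2%, and the result is not reproducible. The error rates in the table apply only if within-arm tests are used to support an efficacy claim. They rest on an assumed equal improvement in both arms, normally distributed changes and 21 evaluable patients per arm. They show what the wording would permit and are not a forecast of what the investigators will do. The correction should be made before analysis because it concerns the test of the primary outcome.

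**What to change.** In section 2.10.1, replace the sentence on paired tests with one stating that the change from visit 2 to visit 4 in A/CS, and in each secondary outcome, will be compared between the YGJT and control groups with the 2-sample t test or the Mann-Whitney test, as section 2.10.2 already does for safety. The Shapiro-Wilk check can stay as planned. Add that paired t and signed-rank tests are descriptive within-group summaries and support no conclusion on efficacy.

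The cost is a sentence or two in the protocol, carried into the statistical analysis plan. It needs no new data and no change to the sample size.
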